## Abstract

**Background:**

Osteoarthritis (OA) is a heterogeneous group of conditions with disturbed integrity of articular cartilage and changes in the underlying bone. The pathogenesis of OA is multifactorial and not just a disease of older people. Hydroxychloroquine (HCQ) is a disease-modifying anti-rheumatic drug (DMARD) typically used for the treatment of various rheumatic and dermatologic diseases. Three studies of HCQ in OA, including one abstract and one letter, are available and use a wide variety of outcome measures in small patient populations. Despite initial evidence for good efficacy of HCQ, there has been no randomized, double-blind, and placebo-controlled trial in a larger patient group. In the European League Against Rheumatism (EULAR), evidence-based recommendations for the management of hand OA, HCQ was not included as a therapeutic option because of the current lack of randomized clinical trials.

**Methods/Design:**

OA TREAT is an investigator-initiated, multicenter, randomized, double-blind, placebo-controlled trial. A total of 510 subjects with inflammatory and erosive hand OA, according to the classification criteria of the American College of Rheumatology (ACR), with recent X-ray will be recruited across outpatient sites, hospitals and universities in Germany. Patients are randomized 1:1 to active treatment (HCQ 200 to 400 mg per day) or placebo for 52 weeks. Both groups receive standard therapy (non-steroidal anti-inflammatory drugs [NSAID], coxibs) for OA treatment, taken steadily two weeks before enrollment and continued further afterwards. If disease activity increases, the dose of NSAID/coxibs can be increased according to the drug recommendation. The co-primary clinical endpoints are the changes in Australian-Canadian OA Index (AUSCAN, German version) dimensions for pain and hand disability at week 52. The co-primary radiographic endpoint is the radiographic progression from baseline to week 52. A multiple endpoint test and analysis of covariance will be used to compare changes between groups. All analyses will be conducted on an intention-to-treat basis.

**Discussion:**

The OA TREAT trial will examine the clinical and radiological efficacy and safety of HCQ as a treatment option for inflammatory and erosive OA over 12 months. OA TREAT focuses on erosive hand OA in contrast to other current studies on symptomatic hand OA, for example, HERO [Trials 14:64, 2013].

**Trial registration:**

ISRCTN46445413, date of registration: 05-10-2011.

## Background

Osteoarthritis (OA) is a heterogeneous group of conditions with defective integrity of articular cartilage and changes in the underlying bone. The pathogenesis is multifactorial and involves a complex interplay of genetic, metabolic, biochemical, and biomechanical factors with variable components of inflammation. Subsets of patients with OA develop an inflammatory and erosive form of the disease. As one of the most prevalent musculoskeletal diseases, the condition leads to pain in and around the affected joints and to swelling, stiffness, deformity, and gradual loss of function [1, 2]. This disease not only affects older people, but also the younger working population. The pathologic mechanisms and its triggers are still not known. Treatment options are limited to symptomatic therapy and (rarely) surgical intervention. Compared to the research results of hip OA and knee OA, there are very few basic research activities in the field of hand OA. However, over the past 15 years, there has been an increase in the number of clinical trials in OA including hand OA. Nevertheless, effective treatments for OA are limited, since many treatments have only small symptom-relieving effects. There are few therapeutic studies in patients with hand OA investigating oral non-steroidal anti-inflammatory drugs (NSAIDs), topical NSAIDs, and other topical drugs. For the symptomatic slow-acting drugs in OA (SYSADOA) and disease modifying drugs in OA (DMOADS), very few studies can be identified, and unfortunately, many publications are available only as abstracts. Most of these randomized controlled trials (RCTs) used a broad range of outcome measures, some of them poorly standardized. Differences in disease definition between studies make it hard to generalize the results for clinical practice. Many studies were underpowered or planned as pilot studies [3, 4]. HCQ (originally an antimalarial drug) is a disease modifying drug (DMARD) used for inflammatory erosive OA in clinical practice. HCQ has been used since the 1950s for the treatment of various rheumatic and dermatologic diseases. Current research has further enhanced our understanding of the pharmacologic mechanisms of these drugs, involving inhibition of endosomal toll-like receptor (TLR) signaling, which inhibits B cell and dendritic cell activation [5]. With this understanding, the use of these medications in rheumatology is broadening.

In OA and hand OA, symptomatic therapy with NSAIDs or coxibs is the most frequently administered treatment. Regarding tumor necrosis factor (TNF)-α-antagonists, one pilot study with adalimumab (ADA) in patients with erosive/inflammatory OA (EOA) of the hands demonstrated that ADA was well tolerated; however, treatment with ADA for three months did not significantly improve signs and symptoms of EOA, and most patients did not achieve an ACR20 [6]. Three studies of HCQ in EOA, including one abstract and one letter, are available. HCQ at a dose of 200 to 400 mg daily was effective in seven patients with evidence of EOA on X-ray. This study was an open retrospective study [7]. The result of an open retrospective study of eight patients with EOA of proximal interphalangeal (PIP) and distal interphalangeal (DIP) joints and a dosage of 400 mg daily demonstrated that in six patients an improvement of synovitis, morning stiffness, and global assessment was seen [8]. One prospective, randomized, double-blind, and placebo-controlled trial in 15 patients with EOA of PIP and DIP joints and radiological changes consistent with OA showed that HCQ was more effective than placebo on clinical (Ritchie-Index) and biological assessments (ESR, IL_2receptor level) [9]. To summarize, the review of published data on hand OA raises more questions than it answers with regard to the evaluation of therapeutic agents in hand OA. Moreover, the few RCTs that have been performed were in small patient populations and lack standardized outcome assessments [4]. A task force of the Osteoarthritis Research Society International (OARSI) recently published guidelines and recommendations for clinical trials in hand OA [10]. Despite initial evidence for good efficacy of HCQ, there has not been a randomized, double-blind, and placebo-controlled trial in a larger patient group. In the European League Against Rheumatism (EULAR) evidence-based recommendations for the management of hand OA, HCQ was not included as therapeutic option because of the current lack of randomized clinical trials [11].

The evidence of HCQ in hand OA has never been investigated in controlled randomized studies, although there are clinical indications for good effectiveness in daily rheumatologic practice. Until now, HCQ is only used for hand OA in daily practice once all other available therapies have failed. HCQ treatment of patients with other rheumatic diseases shows that the drug is very well tolerated if management for the prevention of possible side effects (e.g. retinopathy) is carried out adequately. *In vitro* studies have shown that HCQ decreases the production of TNF-α, IL-6 and IFN-α by mitogen-stimulated peripheral blood lymphocytes [12]. A dose-dependent inhibition of TNF-α, IL-1β, and IL-6 by endotoxin-stimulated whole blood was also noted [13]. Monotherapy of systemic lupus erythematosus (SLE) patients with chloroquine results in a decrease in serum levels of IL-6, IL-18, and TNF-α [14]. It has been suggested that inhibition of TNF-α production by antimalarial drugs, which mainly affect monocytes, may be independent of the lysomotropic action of the drugs and related to nuclear effects [15]. HCQ acts as prostaglandin antagonist by inhibition of phospholipase A2 [16]. Rheumatoid arthritis (RA) and inflammatory OA synovial tissue have a similar pro-inflammatory and anti-inflammatory cytokine profile. OA cartilage shows lower production of proteoglycans, type II collagen, and IL-1β [17]. Moreover, HCQ potentiates Fas-mediated apoptosis of synoviocytes [18]. This background and the knowledge of the effectiveness in RA patients raise the question of whether this drug may also be effective in hand OA. When compared with other immunomodulatory agents, antimalarial drugs have a favorable safety profile. Our understanding of the toxicities and modes of action of these drugs may suggest new applications and modified treatment regimes in hand OA where there is huge unmet clinical need. On the other hand, more studies are needed to further explore the relationship between self-reported and radiographic outcomes and the relationship with other domains such as biomarkers and other imaging modalities [10, 19–21].

The aim of OA TREAT is to investigate the efficacy of HCQ by clinical and radiological outcomes compared to placebo in patients with severe and refractory inflammatory hand OA. The co-primary hypotheses are that patients receiving HCQ have a lower Australian-Canadian OA Index (AUSCAN) score in the dimensions for pain and hand disability at week 52 and that they have a lower rate of radiographic progression from baseline to week 52 compared to patients receiving placebo.

## Methods/Design

### Trial design

The trial is based on a call of investigator initiated trial funding 2009 by the German Ministry of Education and Research (Bundesministerium für Bildung und Forschung [BMBF]) and is carried out with German rheumatologic and statistical stakeholders with experience of treating hand OA. OA TREAT is a multicenter, double-blind, placebo-controlled phase III trial with a parallel group design.

### Study setting

Recruitment aims are based on the design of the study as a national multicenter study and on the established cooperation with primary care physicians within the Regional Collaborative Arthritis Centers (Department of Rheumatology and Clinical Immunology, Charité - Universitätsmedizin Berlin, German Competence Network Rheuma, HIT HARD Trial Network). All selected centers are very experienced in trial performance and approved by the local ethic committees (EC) in their quality management as a clinical trial center. Our partners are listed on our website for study (http://insider.charite.de/projekte/aktuelle_projekte/oa_treat/study_centers/).

### Participants and recruitment

Patients with hand OA according to the classification criteria of the American College of Rheumatology (ACR) with recent X-ray of the hands [22], dating from less than six months and showing radiological signs of digital erosive OA as defined by grades 2 or higher, per the Kellgren and Lawrence scale in one or more joints [23].

Participants must meet the inclusion and exclusion criteria in order to participate. These will be assessed at the screening visit. The key inclusion and exclusion criteria are listed in Table 1.

**Table 1 Tab1:** **Key selected inclusion and exclusion trial criteria for patients**

Key inclusion criteria	Key exclusion criteria
1. Men and women from 40 to 80 years of age.	1. Patients who are currently treated with hydroxychloroquine (HCQ) or have received HCQ in the past due to OA of the hands.
2. Presence of clinical hand osteoarthritis (OA) according to American College of Rheumatology (ACR) criteria.	2. Patients who have not tolerated HCQ (for example, skin disease or malaria prophylaxis) or patients for whom HCQ was discontinued due to an eye disease.
3. Conforming to the ACR criteria for hand OA supported by X-ray of both hands, dating less than 6 months previous, X-ray of the hands showing radiological signs of digital erosive OA in one or more joints. This criterion is checked by a central assessment.	3. Existence of a pain syndrome of the upper limbs, which would interfere with the monitoring of pain.
4. Symptoms of digital inflammatory OA (pressure pain of the joint and/or florid joint swelling and/or redness and/or warmth) with more than three fingers’ joints for more than 3 months (at least every other day) despite taking analgesics and non-steroidal anti-inflammatory drugs (NSAIDs).	4. Patients suffering or having suffered from secondary OA after one of the following disease (for example, infectious arthritis, acromegaly, ochronosis, hemochromatosis, gout, *etcetera*) or inflammatory joint diseases.
5. Pain above 4 as evaluated by the Australian-Canadian OA Index (AUSCAN)-numeric rating score (NRS) (0-10).	5. Planned surgery.
6. Function as co-primary clinical outcome with ≥26 using the AUSCAN.	6. Local injection of finger or hand joints with glucocorticoids or other medications in the previous 3 months.
7. The ability to understand the trial information for patients (Arzneimittelgesetz, German Medicinal Products Act (AMG) §40(1) and 3b).	7. Current intake of oral, intra-articular (i.a.) or systematic glucocorticoids (intravenous (i.v.), intramuscular (i.m.)).
8. The ability to sign the written informed consent form including the data protection form (according AMG §40(1) and 3b).	8. Presence of retinopathy.
	9. Known hypersensitivity to HCQ or to one of the drugs in this study protocol.
	10. Treatment with digoxin
	11. Any unstable medical condition or other serious clinical situations that expose the patient to risk in the opinion of the local investigator.
	12. Current participation in another clinical trial or undergoing an experimental treatment.
	13. Patients who are underage or incapable of understanding the aim, importance and consequences of the study or of giving legal informed consent (according to AMG §40(4) and 42(2) and (3)).
	14. Prisoners and persons who are institutionalized due to AMG §40(1), no. 4
	15. Pregnant and breastfeeding women

A total of 510 patients with erosive and inflammatory hand OA will be recruited and randomly allocated to either the treatment or placebo group. Recruitment methods will include advertisements through the local media and community groups, invitations to previous study participants who have given their consent to be contacted regarding future research projects and liaisons with general practitioners, rheumatologists, orthopedists, and German patients associations (for example, Rheumaliga).

### Intervention

Both groups receive standard therapy (NSAID, coxibs) for OA treatment, taken steadily two weeks before enrollment and continued afterwards (Figure 1). If disease activity increases, the dose of NSAID/coxibs can be increased according to the drug recommendation.Group I receives capsules with 200 to 400 mg HCQ as an oral application from day 1 up to the end of week 52. Group II receives capsules as an oral placebo application from day 1 up to the end of week 52. In both groups, a radiological examination is performed at week 52 (Figure 1). Rescue treatment with acetaminophen (maximum of 4 × 500 mg/d) is possible. Ongoing physiotherapy or occupational therapy before screening can be continued unchanged, but must not be commenced after enrollment.

**Figure 1 Fig1:**
[figure not shown]
**Trial overview.**

The time schedule of enrollment, interventions, trial assessments, and visits for participants is described in Table 2.

**Table 2 Tab2:** **Trial timeline, interventions, assessments and visits of OA TREAT**

Primary outcome measures:	
*Clinical endpoint*	Australian-Canadian Osteoarthritis (OA) Index (AUSCAN, German version) dimensions for pain and hand disability as co-primary clinical outcomes at week 52.
*Radiographic co-primary endpoint:*	Radiographic progression from baseline to week 52.
Key secondary endpoints:	
*Clinical outcomes:*	•Assessment and comparison of the inflammatory status using the following parameters: joint pain and joint swelling, night pain, morning stiffness, local erythema/redness, c-reactive protein (CRP) and erythrocyte sedimentation rate (ESR) levels from baseline to week 26,52.
	•Comparison of the increase or decrease of the consumption in the standard medication in the previous 7 days at each visit (non-steroidal anti-inflammatory drugs (NSAIDs), coxibs).
*Patients-reported outcomes*	•Patients global assessment of disease activity, patient’s assessment of stiffness, and physician’s global assessment of disease activity from baseline to week 26,52.
	•Comparison of pain, functioning, disability, quality of life, patient-acceptable symptoms and health with Health Assessment Questionnaire (HAQ), Short Form for the Changes of Quality of Life (SF-36), Short Form for the Assessment and Quantification of Chronic Rheumatic Affections of the Hands (SF-SACRAH), Australian-Canadian Osteoarthritis Index (AUSCAN), *etcetera* from baseline to week 26, 52.
*Assessment of safety*:	
Safety and tolerability of hydroxychloroquine (HCQ) with reports on adverse events (AE) and serious adverse events (SAE) from screening to baseline and week 12, 26, 39, 52, and follow-up of the eyes will be performed by an ophthalmologist at baseline and every 6 months (week 26 and 52).	

### Outcomes

OA TREAT examines a number of clinical, radiographic and patient-reported outcomes. These are listed in Table 3.

**Table 3 Tab3:** **Primary and secondary outcomes of OA TREAT**

	Enrollment -30 days	Allocation/baseline 0	Post-allocation				Close-out week 52	Follow-up +28 days
Time point			Day 0	Week 13	Week 26	Week 39		
**Enrolment: Eligibility screen**	X							
**Informed consent**	X							
**Key investigations**								
•Medical history								
•Medication history								
•Clinical, laboratory and immunological investigation								
•Pregnancy test								
•X-ray of both hands and assessment by two blinded reviewers	X							
•Ophthalmological examination								
•AUSCAN Index								
•Patient-reported outcomes (HQA, SF-36, SF-SACRAH)								
**Allocation**		X						
**Interventions:**								
• Hydroxychloroquine			X*	X*	X*	X*	X*	
• Placebo			X*	X*	X*	X*	X*	
**Assessment:**								
**Baseline variables:**								
•Medical history								
Medication history								
•Clinical, laboratory and immunological investigation		X						
•AUSCAN-Index								
•Patients-reported outcomes (HAQ, SF-36, SF-SACRAH)								
•Safety (AE, SAE)								
•Accompanying research*								
**Outcome variables**								
•AUSCAN			X	X	X	X	X	
•X-ray of both hands							X	
Medication history								
•Laboratory and immunological investigation			X	X	X	X	X	
•Patient-reported outcomes								
•Accompanying research								
•Safety (AE, SAE)			X	X	X	X	X	X

X*: The therapy is administered continuously from day 1 to week 52.

AUSCAN: Australian-Canadian OA Index (German version) for pain and hand disability. The patient-centered self-administered AUSCAN Index is a valid, responsive and feasible tri-dimensional (pain, stiffness, and function) index developed specially for hand osteoarthritis studies [24–26].

HAQ-DI: Health Assessment Disability Index. The HAQ-DI assesses the degree of difficulty experienced in eight categories of daily living activity using 20 questions. This questionnaire has been validated for rheumatoid arthritis (RA); there is no experience in OA hand trials.

SF-SACRAH: Short Form Score for the Assessment and Quantification of Chronic Rheumatic Affections of the Hands. The SACRAH includes visual analog scales covering the extent of hand function, stiffness and level of pain from 0 to 100 [27]. The smallest number of questions of the modified score for the assessment and quantification of chronic rheumatic affections of the hands (M-SACRAH) providing reasonable reliability was identified by factor analysis and calculating Cronbach’s alpha, subsequently resulting in a five-item scale, the short form-SACRAH (SF-SACRAH) [23, 27].

SF-36: Short form for the Changes of Quality of Life. The SF-36 v.2 is a 36-item generic health status measure. It measures eight general concepts: physical functioning, physical role, bodily pain, general health, vitality social functioning, emotional role and mental health. These concepts can also be summarizes as physical (PCS) and mental component (MCS) scores. This questionnaire should be completed by the subject prior to any procedures being performed at the visit, if possible. To date, there is no experience in OA hand trials. Examples of health-related quality instruments include the SF-36 [28].

AE: Adverse events.

SAE: Severe adverse events.

*: Accompanying research of biomarkers in hand OA, dental and periodontal disease, health economic cost analysis.

### Methodological aspects

#### Sample size

Our sample size considerations are based on the EULAR recommendations for the planning of RCTs in patients with hand OA [13]. We considered differences in change scores in the AUSCAN scales pain and hand function, which were observed in RCTs comparing NSAIDs (lumiracoxib or ibuprofen) with placebo as clinically relevant differences that also should be detected with a sufficient power in this RCT. For these reasons, we aim to detect an effect size (ES) of 0.4 for pain (SD: 4.3) and of 0.25 for function (SD: 7.3) [13, 29]. An ES of 0.25 is also considered to be relevant for changes in the radiographic scores. Based on these assumptions, a sample size of n=255 per group is sufficient to achieve a power of 95% for the multiple endpoint test (first primary hypothesis) and an 80% power for the second primary endpoint (radiographic progression). The sample size is also sufficient to achieve an at least 80% power when comparing the two AUSCAN subscales pain and hand function separately.

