#### Study termination

Patients will be informed that they have the right to withdraw from the study at any time for any reason, without prejudice to their medical care. The investigator also has the right to withdraw patients from the study for any of the following reasons (but each patient with one application of HCQ and who is followed to X-ray investigation of the hands at week 52 is included in the trial analyses):Intercurrent diseases.Ophthalmologic changes associated with HCQ.Occurrence of any grade 3 to 4 WHO toxicity or an unacceptable adverse event.A treatment delay or interruption of *>*2 weeks because of toxicity.Patient request.Noncompliance.General or specific changes in the patient’s condition unacceptable for further treatment in the judgment of the investigator.Protocol violations.Medical and ethical discretion of principal investigator.Failure to return for follow-up.

The whole trial may be stopped for the following:Administrative reasons.Incidence of severe adverse events or fatal adverse events. Stopping rules are decided jointly by the data monitoring and safety board.

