The following potential limitations of the study should be noted: generalizability of the results may be limited by specific inclusion and exclusion criteria, and results may not apply to the entire target population. However, selection criteria were kept as broad as possible to ensure maximal generalizability. For ethical reasons, changes in the NSAID dosages including new treatment starts or treatment terminations are allowed. Since an imbalance in the use of co-medications might have an influence on the outcome in the clinical parameters, the use of NSAID/analgesics is recorded at each study visit and will be analyzed as a secondary outcome. In case there is any imbalance, we anticipate an increased use of co-medication in the placebo group, which could weaken the differences between both treatment arms especially regarding the AUSCAN scales for pain and hand function. However, even if this increased use of NSAIDs/analgesics would reduce the assumed effect sizes for both scales by 25%, the power of the multiple endpoint test comparing the first primary outcome will be greater than 80%. In the unlikely case of an increased use of NSAIDs and/or analgesics in the verum arm, this observation will be considered in the interpretation of the findings to discuss the possibility of a false positive result.

HCQ has been used since the 1950s for the treatment of various rheumatic and dermatologic diseases. It is also used for inflammatory erosive OA in clinical practice, but there are no high-quality clinical trials to support its use in hand OA. Three pilot studies of HCQ in EOA are available, but their results are contradictory, population sizes are small, and there is a lack of standardized outcome measures. Despite a favorable safety profile and initial evidence for good efficacy of HCQ, there has not been a randomized, double-blind, and placebo-controlled trial in a larger patient group. HCQ was therefore not included as a therapeutic option in the EULAR evidence-based recommendations for the management of hand OA [11]. To close this gap, we are currently performing the trial OA TREAT to investigate the efficacy of HCQ by clinical and radiological outcomes compared to placebo in patients with severe and refractory inflammatory hand OA. In contrast to other current studies on symptomatic hand OA, for example, HERO [34], OA TREAT focuses on erosive hand OA, a more severe subset of hand OA with very limited therapy options.

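### The 80% power for radiographic progression assumes essentially complete week-52 X-rays: the 510 patients randomised are exactly the 2 × 255 in the power calculation, with no allowance for missing films

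*Protocol article*

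**What the plan says.** The Sample size section gives effect sizes of 0.4 for AUSCAN pain and 0.25 for AUSCAN function. It adds: "An ES of 0.25 is also considered to be relevant for changes in the radiographic scores". On that basis, "a sample size of n=255 per group is sufficient to achieve a power of 95% for the multiple endpoint test", and the same number is said to give "an 80% power for the second primary endpoint (radiographic progression"). A further sentence claims "at least 80% power when comparing the two AUSCAN subscales pain and hand function separately".

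The number to be enrolled is under Participants and recruitment, after Table 1: "A total of 510 patients with erosive and inflammatory hand OA will be recruited and randomly allocated". The Abstract gives the same total.

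Three other places bear on who will have a week-52 film:

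- Intervention and Table 3 schedule one X-ray after baseline, at week 52.
- Study termination lists reasons for withdrawal, one of which is "Failure to return for follow-up". It also says that a patient who has had one application and is followed to the week-52 X-ray is included in the analyses.
- Statistical methods puts every patient who received a dose into the modified intention-to-treat set.

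No attrition rate and no inflation of the sample size appear.

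**The concern.** A power statement refers to patients who contribute an outcome; a recruitment target refers to patients randomised. Here they are the same number, so the stated radiographic power holds only if nearly everyone randomised has a readable film a year later. Because week 52 is the only film after baseline, a patient lost before then contributes no observed progression at all. Membership of the modified intention-to-treat set does not change that.

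Radiographic progression is a co-primary hypothesis and the trial's structural question. It has the thinnest margin of the stated powers for the primary hypotheses, and it is not covered by the one power sensitivity in the article, the 25% effect reduction in the Discussion, which concerns AUSCAN only. A null radiographic result would be read as coming from an 80%-powered test when the actual power was some points lower.

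**Working it through.** **Inputs.** From the article: 255 per group, 1:1 allocation, radiographic effect size (ES) 0.25, 5% level. The radiographic hypothesis is tested at full level once the AUSCAN test is significant. Assumed: a two-sided test, because sidedness is not stated; and the proportion *d* of week-52 films missing, because no rate is given (range 5–20%, equal in both arms).

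**Step 1: reproduce the stated figure.** Required number per arm, normal approximation:

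n = 2 × (1.960 + 0.842)² / 0.25² = 251.2, so 252. The exact noncentral t calculation gives 253 (252 per arm has 79.98% power, 253 has 80.14%).

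Power at 255 per arm: Φ(0.25 × √(255/2) − 1.960) = Φ(0.863) = 80.6%; noncentral t, 80.4%.

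The stated 80% is therefore correct for 255 **evaluable** patients per arm. A one-sided 5% test would need only 198–199 per arm and would have 88.1% power at 255. The two-sided, zero-loss calculation is the one that matches.

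**Step 2: the margin.** 255 − 253 = 2 patients per arm, and 2/255 = 0.8% (1.2% using 252).

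**Step 3: power with missing films.** Evaluable per arm m = 255 × (1 − d); power ≈ Φ(0.25 × √(m/2) − 1.960), shown beside the noncentral t value.

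| Missing films d (assumed) | m per arm | Power, normal | Power, t |
|---|---|---|---|
| 0% | 255 | 80.6% | 80.4% |
| 5% | 242.3 | 78.6% | 78.4% |
| 10% | 229.5 | 76.4% | 76.2% |
| 15% | 216.8 | 74.0% | 73.8% |
| 20% | 204 | 71.4% | 71.2% |

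Power stays within 2 points of 80% until about 6% loss. To hold 80% by recruitment, 252–253 evaluable per arm would mean randomising 280–282 per arm at 10% loss (252/0.9 to 253/0.9) and 315–317 at 20%.

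**Step 4: AUSCAN function (ES 0.25).** Without covariate adjustment the numbers are those in the table. But Statistical methods compares function by ANCOVA with the baseline value as covariate. If the SD of 7.3 is that of a change score, the ratio of ANCOVA to change-score variance is (1 − r²)/(2(1 − r)) = (1 + r)/2, where r is the baseline to week-52 correlation (not given). Replacing m by m/((1 + r)/2):

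- r = 0.3: 91% at 10% loss, 88% at 20%.
- r = 0.5: 87% at 10% loss, 83% at 20%.
- r = 0.7: 83% at 10% loss, 78% at 20%.

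**Step 5: the other stated powers.** Pain (ES 0.4) keeps at least 98% up to 20% loss. For the multiple endpoint test, the standardised sum has ES (0.40 + 0.25)/√(2(1 + ρ)). At 15% loss its power is 93–99% for assumed pain–function correlations ρ of 0.9 down to 0.3.

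**The case against.** **The figure reproduces, and the shortfall is conditional.** This stands. There is no arithmetic error, and the article gives no attrition rate, so every figure below 80% rests on an assumed one. At 5% loss the shortfall is under 2 points.

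**The withdrawal list is weak evidence of missing films.** This partly stands. A reader might count every listed reason as lost data. The documents do not support that: a patient taken off treatment for toxicity or noncompliance can still be followed to the week-52 X-ray and analysed. Failure to return, and possibly patient request, are the items that clearly cost the film. But the margin is only two patients per arm.

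**Covariate adjustment may restore power.** For function this stands (step 4), so one cannot say that the claim for function fails. The radiographic test is also an ANCOVA, but the article names no covariate for it and credits no gain. By the same ratio, full recovery would need (1 + r)/2 ≤ 229.5/253 = 0.907, or r ≤ 0.81, at 10% loss, and ≤ 204/253 = 0.806, or r ≤ 0.61, at 20%. No r is given.

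**Stronger readings that a reader might infer:**

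- *The rank-based test loses further power.* An efficiency of 0.955 (78.8% power at 255) holds for normal data only. With skewed scores efficiency can exceed 1; at an illustrative 1.1, power would be about 84% with no loss. The article gives no score distribution, so the direction is unknown.
- *The real power is 0.95 × 0.80 = 76% because the AUSCAN test comes first.* Quoting power per hypothesis is conventional in a hierarchical procedure, the order of testing is disclosed, and the product assumes independence.
- *The Discussion's claim of more than 80% power after a 25% effect reduction is wrong.* With full data it holds up to ρ of about 0.92, and with 10% loss up to about 0.73. To fail it needs either a very high correlation or a high correlation combined with dropout, and the article gives neither quantity.

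**Conclusion.** The point holds for radiographic progression. The stated 80% belongs to 255 evaluable patients per arm, yet 255 per arm is also the number randomised, so a loss of more than about 1% of week-52 films takes power below the stated value. Under assumed losses of 5, 10, 15 and 20%, power is about 78, 76, 74 and 71% (two-sample t approximation, two-sided 5%, no covariate gain credited, as in the article's own figure).

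For AUSCAN function the same margin applies only if no gain from baseline adjustment is credited, so that statement needs a condition. Pain alone and the 95% for the first primary hypothesis are not in question: the latter stays at 93% or more at 15% loss over the correlations tried.

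The weight is moderate. A stated property of a co-primary test depends on unstated complete follow-up, but the likely shortfall is some 4 to 9 points at 10–20% loss, and the design itself need not change.

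**What to change.** Keep N = 510 and amend the Sample size section as follows:

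1. Say that 80% power for radiographic progression (ES 0.25, two-sided 5%) requires at least 253 patients per arm with an evaluable week-52 X-ray.
2. Say that no allowance for missing films is included in the 510, and give the radiographic power as about 76% if 10% of films are missing and about 71% if 20% are, labelled as assumed rates.
3. State the sidedness of the test.
4. For AUSCAN function, say that the claim of at least 80% holds either with nearly complete week-52 data or with the gain from baseline adjustment, and give the baseline correlation relied on. Do not restate it as failed.

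The Discussion sentence on the 25% effect reduction and the order of testing need no correction on this account.

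The cost is a few sentences and a less favourable radiographic figure. No extra patients and no change to the analysis are needed.
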